## Abstract

**Background:**

A vision center (VC) is a significant eye care service model to strengthen primary eye care services. VCs have been set up at the block level, covering a population of 150,000-250,000 in rural areas in North India. Inadequate use by rural communities is a major challenge to sustainability of these VCs. This not only reduces the community’s vision improvement potential but also impacts self-sustainability and limits expansion of services in rural areas. The current literature reports a lack of awareness regarding eye diseases and the need for care, social stigmas, low priority being given to eye problems, prevailing gender discrimination, cost, and dependence on caregivers as factors preventing the use of primary eye care.

**Objective:**

Our organization is planning an awareness-cum-engagement intervention—door-to-door basic eye checkup and visual acuity screening in VCs coverage areas—to connect with the community and improve the rational use of VCs.

**Methods:**

In this randomized, parallel-group experimental study, we will select 2 VCs each for the intervention arm and the control arm from among poor, low-performing VCs (ie, walk-in of ≤10 patients/day) in our 2 operational regions (Vrindavan, Mathura District, and Mohammadi, Kheri District) of Uttar Pradesh. Intervention will include door-to-door screening and awareness generation in 8-12 villages surrounding the VCs, and control VCs will follow existing practices of awareness generation through community activities and health talks. Data will be collected from each VC for 4 months of intervention. Primary outcomes will be an increase in the number of walk-in patients, spectacle advise and uptake, referral and uptake for cataract and specialty surgery, and operational expenses. Secondary outcomes will be uptake of refraction correction and referrals for cataract and other eye conditions. Differences in the number of walk-in patients, referrals, uptake of services, and cost involved will be analyzed.

**Results:**

Background work involved planning of interventions and selection of VCs has been completed. Participant recruitment has begun and is currently in progress.

**Conclusions:**

Through this study, we will analyze whether our door-to-door intervention is effective in increasing the number of visits to a VC and, thus, overall sustainability. We will also study the cost-effectiveness of this intervention to recommend its scalability.

**Trial Registration:**

ClinicalTrials.gov NCT04800718; https://clinicaltrials.gov/ct2/show/NCT04800718

**International Registered Report Identifier (IRRID):**

DERR1-10.2196/31951

## Introduction

Primary care is the cornerstone of the global health system and is rooted in the 1978 Declaration of Alma Ata [1], encompassing disease prevention and the equitable distribution of health care [2]. Derivative to this, the Global Action Plan for Universal Eye Health [3] emphasizes the importance of providing basic eye care to all individuals, and the communities they constitute, at affordable rates [4]. An application of the bottom-up approach, primary eye care is an integral part of comprehensive eye care: promoting eye health, increasing accessibility, and linking individuals and the community to health care systems [5-8].

In India, primary eye care is delivered through two main mechanisms:

Transient screening camp-scheduled, community-based activities that screen patients, provide glasses to those requiring them at the camp itself, and transport those needing surgery to the base hospital [9].Permanent facilities: Vision centers (VCs) with catchment areas of roughly 50,000 people, mostly located in rural areas and urban slums and accessible by public transport [10,11]. They refract, diagnose, and treat minor eye conditions and refer cases needing further care to their nearest base hospital [12].

Globally, awareness regarding eye health [13], need-based demand [13], financial issues and cost [13,14], and poor communication from providers [14] are the major barriers to primary eye care use. The literature on barriers to primary eye care in India is limited but points to a lack of knowledge about eye diseases, detrimental social stigmas, low priority being accorded to eye problems, gender discrimination, unaffordability, a lack of perceived need, and immobility and dependence on escorts [15-18]. These barriers to the access and use of services have the potential to affect the overall operational sustainability of the VCs, affected in large part by the number of walk-in patients [19].

Our organization is a network of eye care delivery mechanisms based on the pyramidal model [10] and spread across North India. Currently, 36 VCs (9 urban and 27 rural) are under operation, raising awareness; providing refraction, recognition, and referral services to their catchment population; and increasing contact of those in need of services with doctors through teleophthalmology. For the majority of people, these primary eye care centers are the first point of contact when accessing or attempting to access eye care services. Moreover, gender differences have been established in the use of VC services, with the proportion of women among the walk-in patients being higher compared to men in urban VCs and lower in rural ones [12].

Thus, generating awareness, developing trust, and improving access to these VCs, amongst the entire catchment population they service, is essential not only for the overall sustainability of these centers but also to bring more and more people under the ambit of primary care delivery. Previously, a door-to-door screening model was posited to eliminate avoidable blindness [15]. This research protocol aims to study the effect of an intervention combining door-to-door screening with regular awareness activities in the catchment population on service use at VCs. The overall cost-effectiveness of such an intervention will also be analyzed.

## Methods

### Study Design and Process

This study is a randomized, parallel-group experimental study in which we selected four VCs, two each in the intervention and control arms (one each from a particular operational area).

Our organization has six secondary centers, of which four are located in the state of Uttar Pradesh, namely Meerut, Mathura, Saharanpur, and Kheri. These regions have a total of 23 VCs operating in rural and semiurban areas, together serving around 1 million people. Of these four secondary centers, two were selected (Vrindavan in Mathura District and Mohammadi in Kheri District) for this study based on feasibility and the demographic profile of their catchment population.

The Vrindavan region has eight VCs delivering eye care services in its semiurban areas, while the Mohammadi region has six VCs (five rural and one semiurban). Most of these VCs have been operational for over 3 years. However, data from the previous year indicated that 80% of the VCs are suboptimal in their performance. The VCs performing suboptimally were listed. From a total of 10 VCs (5 in each region, meeting the inclusion/exclusion criteria), 2 were randomly selected from each region using the RAND function in Microsoft Excel (ie, 1 each for the control and the intervention arm). The process is illustrated in detail in Figure 1.

**Figure 1 figure1:**
[figure not shown]
Selection process used to identify the study vision centers (VCs). OPD: outpatient department.

The VCs in the two blocks of Mathura District are located at Chhata and Raya, while the two VCs in the two blocks of Kheri District were located at Mitauli and Pashgaon. Due to the nature of the study, it was not possible to mask the field staff to the intervention.

### Inclusion/Exclusion Criteria

The regional team gathered detailed information regarding all VCs operating in the Vrindavan and Mohammadi regions. VCs were included in the study based on the following inclusion criteria:

Low performance (walk-in OPD ≤ 10 per day)Duration of operation > 1 yearPresence of one VC in each arm from selected VCs

VCs with walk-in outpatient department (OPD) numbers greater than 10 per day and those in operation for less than 1 year were excluded.

### Study Setting

Mathura District has a population of about 2.5 million, 70% of whom are resident in rural areas [20]. Kheri District has a population of around 4 million, of which 88% reside in rural areas [21].

Per our existing data, around 75% of the patients visiting our VCs in these 2 districts reside within 10 km of our VCs. The Chhata block, in Mathura, has 81 villages, with around 30 of those being within 10 km of the VC. These 30 villages have a combined population of around 70,000. In contrast, the Raya block has 124 villages, with around 90 of these being within 10 km of the VC, having a combined population of around 130,000.

In Kheri District, the Mitauli block has 138 villages, of which 75 are within 10 km of the VC. The combined population of these villages is around 111,000. The Pashgaon block has 230 villages, with around 85 of these being within 10 km of the VC, having a combined population of around 110,000.

### Sample Size

The average OPD attendance at the intervention centers is 7 per day at present. We expect to achieve 14 after the intervention, failing which, the intervention will not be considered a success. Therefore, the primary objective of the statistical analysis would be to estimate the average attendance, postintervention, with extreme precision, which will lead us to assess whether we have been able to achieve the target (14 per day, on average). We set the confidence interval (CI) to ±1 for the postintervention sample mean (the narrowest-possible CI in this case). To check whether at least 20 per day on average has been achieved, we expect a sample mean of at least 21 (ie, the CI will be 20-22). The number 20 has been determined based on a feasibility study conducted to project VC sustainability. We assume that the probability of the CI is 95% and the daily OPD attendance has a Poisson distribution. Thus, we expect that the postintervention daily attendance will have a Poisson distribution with a mean of at least 21. This implies that the variance of the distribution will also equal 21 (or more), and we want to estimate the mean with a 95% CI of ±1. This requires a minimum sample size of 81 days.

We used the following formula to calculate the sample size:

Sample size = (1.96^2^/*d*^2^) × Variance of the distribution

where 1.96 is the 97.5 percentile point of the standard normal distribution and d is the length of the CI (on one side of the estimate). If d = 1 and variance = 21, we obtain sample size = 81. We set a target of 20 per day in the pre-CODIV-19 time, but due to the pandemic, we revised our desired target to 14 per day to consider the intervention a success. We persisted with the additional days in the sample size (instead of 58 days for a target of 14) to be able to estimate up to 14 per day OPD attendance with precision.

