#### Cost-Effectiveness Analysis

Cost-effectiveness analysis and incremental cost-effectiveness analysis will be performed, and the incremental cost for every additional beneficiary attending the VC will be calculated. To calculate the increase in the number of patients, the average number of patients visiting per day during the same months in the previous year will be subtracted from the average in the study period. A change in the control VCs, if any, will be further deducted from this before using this as the denominator for calculating cost-effectiveness.

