### Outcomes

The primary outcome for this study will be an increase in the number of walk-in patients at the VCs from baseline (7-8 walk-in patients to 14 per day after the intervention period of 4 months). The secondary outcomes will be uptake of spectacles and uptake of surgery among those advised. If the intervention proves effective in terms of the number of people visiting the VCs, cost-effectiveness will also be a secondary outcome.

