### Limitations

Although we randomly selected the VCs from our two operational regions, the fact that we operate only in North India can be one limitation of our study. We had planned this study before the COVID-19 pandemic, and even after reasonable delay due to the unrelenting nature of the pandemic, we plan to start this study during the ongoing pandemic. Due to this, the target for the number of patients visiting the VCs has reduced. Although the conditions may not be near normal during data collection, we do not anticipate any difference in the way in which the intervention and control VCs would be affected by the prevalent conditions. Due to the nature of the intervention, it is not possible to mask the personnel on ground, and this may bring in some short-term behavior change, which may not be sustained. Another limitation of our study would be the short duration of data collection following the intervention. To analyze the long-term impact of the intervention, another study will be planned subsequently in case the results of this study show a positive impact.

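### The 14-per-day success rule has no control term and is not reconciled with the planned between-arm comparison

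*Protocol article*

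**What the plan says.** Sample Size gives the starting level ("The average OPD attendance at the intervention centers is 7 per day at present") and then the rule: "We expect to achieve 14 after the intervention, failing which, the intervention will not be considered a success". It repeats the rule when explaining the pandemic change from 20: "we revised our desired target to 14 per day to consider the intervention a success". The same section says that the "primary objective of the statistical analysis would be to estimate the average attendance, postintervention, with extreme precision", and it derives the number of days from the precision of that single mean. Outcomes states the primary outcome as an increase "from baseline (7-8 walk-in patients to 14 per day after the intervention period of 4 months". None of these statements mentions the control VCs.

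The controls do appear elsewhere. Data Analysis plans a Z test for proportions, at the 5% level, comparing the change in walk-ins between the arms. Cost-Effectiveness Analysis measures the increase against the same months of the previous year and then says: "A change in the control VCs, if any, will be further deducted from this before using this as the denominator". Limitations, on the pandemic, says "we do not anticipate any difference in the way in which the intervention and control VCs would be affected by the prevalent conditions".

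**The concern.** An absolute level in one arm mixes the intervention effect with whatever else moves attendance. The VCs were eligible because attendance was low (at most 10 per day), and the study runs during a pandemic that had already led the sponsor to cut the target. The expectation that both arms will be affected alike protects the conclusion only if the control change is subtracted. The cost-effectiveness analysis subtracts it; the success rule does not.

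At stake is the headline answer. The 14-per-day rule, the between-arm test and the control-adjusted increase can point in different directions on the same data, and the article gives no order of precedence. Outcomes also makes cost-effectiveness a secondary outcome only if the intervention proves effective, so the choice of criterion may decide whether that result is reported.

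**Working it through.** **Inputs from the article.** Intervention baseline 7 per day; target 14 per day, previously 20; half-width d = 1; variance 21; 81 days, or 58 for the lower target; two VCs per arm, one per region. On the model: "We assume that the probability of the CI is 95% and the daily OPD attendance has a Poisson distribution".

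**Step 1: reproduce the sample size.** n = (1.96²/d²) × variance.
- Variance 21: 3.8416 × 21 = 80.67, so 81 days. Reproduced.
- Variance 15 (14 plus the half-width of 1, as 21 is 20 plus 1): 3.8416 × 15 = 57.62, so 58 days. Reproduced.

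Both figures describe the precision of one mean in one arm. No control quantity enters.

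**Step 2: fail direction.** Take a true doubling, 7 × 2 = 14, multiply by a common downturn, and find the exact Poisson probability that the mean of 81 days is at least 14.

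| Common change | True mean | P(observed mean ≥ 14) |
|---|---|---|
| none | 14.0 | 0.50 |
| −5% | 13.3 | 0.044 |
| −10% | 12.6 | 0.0003 |
| −30% | 9.8 | about 0 |

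If instead the lower 95% limit must reach 14, which is how the section reasons for 20 (expected mean 21, interval 20 to 22), the observed mean must be about 14.84. An undisturbed doubling then passes with probability only 0.02.

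**Step 3: pass direction, zero intervention effect.** The same calculation with only background growth from 7.

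| Background factor | True mean | P(mean ≥ 14) | P(lower limit ≥ 14) |
|---|---|---|---|
| 1.43 | 10.0 | about 0 | about 0 |
| 2.0 | 14.0 | 0.50 | 0.02 |
| 2.1 | 14.7 | 0.95 | 0.38 |
| 2.2 | 15.4 | above 0.99 | 0.90 |

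A pass with no effect therefore needs background attendance to about double. Two checks on how likely that is:
- *Recovery.* If the target cut measures the pandemic effect (assumption), 14/20 = 0.70 and full recovery lifts 7 to 7/0.70 = 10, not 14.
- *Regression to the mean.* For a VC observed near 7, with assumed period-to-period SDs of 0.5 to 4 per day (assumed VC means averaging 10 to 12, SD 3 to 4), the expected next value is 7.1 to 9.5 and the chance of 14 or more is 0% to 18%.

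**Step 4: the realistic pass-side error.** With recovery to 10, the intervention needs a multiplier of only 14/10 = 1.4 to reach the target, instead of 14/7 = 2.0. With an assumed control baseline of 7, the net change is (14 − 7) − (10 − 7) = +4 per day, where the one-arm reading gives +7.

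**Step 5: what a control-adjusted rule can deliver.** With Poisson variation only and 2 × 81 = 162 VC-days per arm and period (81 baseline days per VC assumed), SE = √[(7 + 14 + 7 + 10)/162] = 0.484, so +4 has a 95% CI of 3.05 to 4.95. This is too narrow because it ignores variation between VCs. Using the two regional differences D₁ and D₂ instead, the SE of their mean is |D₁ − D₂|/2 on 1 degree of freedom, with t about 12.7. The half-width is 12.7 × |D₁ − D₂|/2 = 6.35 × |D₁ − D₂|. A net +4 excludes zero only if the two regions agree to within 4/6.35 = 0.63 per day. Poisson noise alone gives D₁ − D₂ an SD of √(2 × 38/81) = 0.97.

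**The case against.** The control arm is not ignored. Data Analysis plans a between-arm test of the change in walk-ins, and the cost-effectiveness denominator is control-adjusted. A reader might infer that the trial is assessed only by an uncontrolled before-after comparison; those two sections do not support that. What stands is narrower: neither analysis is connected to the success rule.

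The first statement of the rule is a necessary condition. Missing 14 means no success, but it does not say that reaching 14 is enough. The later restatement is looser. This weakens any claim that the article commits itself to declaring success at 14. It leaves the fail side untouched, because a clear between-arm benefit at 13 per day would still not count as success.

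A reader might also infer that pandemic recovery or regression to the mean could by itself pass an ineffective intervention. The documents do not make that likely. It needs a doubling, the article's own target revision suggests recovery to about 10, and selection was mild, since 10 of the 14 VCs in the two regions were eligible and four were drawn at random. If low performance was identified from the previous year and the 7 is a later figure, some regression had already happened.

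Finally, an absolute target has a reason: the figure of 20 came from a feasibility study on VC sustainability, which is a question of volume. That supports keeping 14 as an operational target. It does not support using it as the test of whether the intervention works.

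**Conclusion.** The point holds in this form: the success criterion, the primary statistical objective, the sample size and the primary outcome target rest on the intervention VCs' post-intervention mean against a fixed 14 per day. The planned between-arm and control-adjusted analyses are left unlinked to that rule, with no order of precedence.

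The fail side is the stronger part. Under the article's Poisson assumption, a common downturn of 5% to 10% reduces the chance that a true doubling is recognised from 0.50 to between 0.044 and 0.0003. On the pass side the realistic risk is inflation: a net +4 can be read as +7, assuming a control baseline of 7 (the article gives 7 for the intervention centers only) and a recovery to 10. The probabilities are for one series of 81 days with no extra-Poisson variation.

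**What to change.** In Sample Size and Outcomes, define the primary effect as the change in mean daily attendance in the intervention VCs minus the change in the control VCs. Measure both from one common baseline, the same months of the previous year, as Cost-Effectiveness Analysis already does; this replaces the present-day 7 and the 7-8. State that this quantity governs the conclusion on effectiveness, including the condition that triggers the cost-effectiveness outcome. Keep 14 per day as a separate sustainability target, reported alongside.

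Report the net change within each region and overall, with an interval that allows for between-VC variation. Do not make exclusion of zero the success rule on day-level Poisson variance. Describe the 81 days as one-arm precision only.

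The attendance data are already to be extracted for both arms, so no new collection is needed. The real cost is in inference: two VCs per arm give two regional differences and 1 degree of freedom, so the interval will be very wide and the conclusion on effectiveness will be largely an estimate. The article should say so.

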#### Data Analysis

The collected data will further be tabulated and analyzed by each study arm: distance of the village, age, gender, eye issues, visual acuity, compliance with treatment (medicine, surgery, glasses), and revenue and expenditure of VCs. The difference from baseline in the number of walk-in patients, referrals, uptake of services, and costs involved in intervention will be analyzed. The Z test for proportions will be performed to compare the change in walk-in patients between the two arms. *P*<0.05 will be considered statistically significant. Subgroup analysis with respect to age and gender will also be carried out.

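### Vision centers are randomised two per arm, but the arm comparison at P<0.05 rests on visit or day counts; the 81 days and ±1 give no precision for that comparison

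*Protocol article*

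**What the plan says.** **Allocation.** In Study Design and Process: "we selected four VCs, two each in the intervention and control arms (one each from a particular operational area"). The same section gives the pool: "From a total of 10 VCs (5 in each region, meeting the inclusion/exclusion criteria), 2 were randomly selected from each region". Six eligible VCs were therefore not selected.

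**Sample size.** The section starts from the intervention VCs: "The average OPD attendance at the intervention centers is 7 per day at present". The success criterion is an absolute level in that arm: "We expect to achieve 14 after the intervention, failing which, the intervention will not be considered a success". Precision is fixed for one quantity: "We set the confidence interval (CI) to ±1 for the postintervention sample mean". With Poisson days and a mean of 21 it concludes: "This requires a minimum sample size of 81 days". It uses no control rate, arm difference, power or VC-to-VC variation, and does not say whether the 81 days are per VC or per arm.

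**Analysis.** The Data Analysis section compares the arms on change in walk-ins with a Z test for proportions. Its threshold is a P value for which less than "0.05 will be considered statistically significant". The VC is not mentioned as a unit of analysis.

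**The concern.** The quantity that was sized (one arm's mean) is not the quantity that is tested (the difference in change between arms). A test on visits or days treats each as an independent piece of evidence about the intervention. Only four units were allocated, and all days at one VC share whatever happens there: a closure, a staffing change, a local outbreak.

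With one VC per arm per region, such a shock cannot be separated from the intervention, and counting more days makes it look more significant, not less. The Limitations section expects pandemic conditions to affect both arms alike, but two VCs per arm give little to check that against. The result is meant to inform scale-up, and the control change is also subtracted in the cost-effectiveness denominator, so a spurious difference would carry through to both.

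**Working it through.** **1. The plan's own figures.** Formula: n = 1.96² × variance / d².
- Variance 21, d = 1: 3.8416 × 21 = 80.67, so 81 days. Reproduced.
- Variance 15 (target 14 plus 1), d = 1: 57.62, so 58 days. Reproduced.

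**2. What ±1 can describe.** At the revised target of 14 per day, with independent days:

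| Variance | 81 days | 162 VC-days (81 at each of two VCs) |
|---|---|---|
| Poisson | ±0.81 | ±0.58 |
| 2 × Poisson | ±1.15 | ±0.81 |
| 3 × Poisson | ±1.41 | ±1.00 |

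Each entry is 1.96 × √(f × 14 / days), with f = 1, 2 or 3. The values of f are assumptions. Autocorrelation between days would widen all of them.

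**3. Randomisation P with four VCs.** One of two VCs treated in each of two regions gives 2 × 2 = 4 allocations. Each has a mirror image, so the smallest two-sided P is 2/4 = 0.50 (one-sided 1/4 = 0.25). The number of days does not enter.

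**4. False-positive rate of a day-level test on change.** Assume no effect, mean 7 per day, 81 Poisson days per VC in each period, and VC-level change with CV k.
- Variance that the test sees for the difference in change: (7 + 7)/81 per VC, averaged over two VCs and summed over two arms = 14/81 = 0.173.
- Variance that it omits: (7k)².
- Rejection rate = P(|Z| > 1.96 × √(0.173 / (0.173 + (7k)²))).

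| k (assumed) | (7k)² | Effective cut-off | False-positive rate |
|---|---|---|---|
| 5% | 0.1225 | 1.50 | 13% |
| 10% | 0.49 | 1.00 | 32% |
| 20% | 1.96 | 0.56 | 58% |
| 30% | 4.41 | 0.38 | 70% |

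A simulation of 40,000 null trials per row agrees to within 1 percentage point. Taking change from baseline is already built in, so baseline adjustment does not cure the problem.

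**5. A VC-level analysis.** Take 14 v 7 per day after and 7 v 7 before, 81 days per VC per period, and an assumed VC-level SD of change of 1 per day.
- SE = √((14 + 7 + 7 + 7)/(2 × 81) + 1²) = √(0.216 + 1) = 1.10.
- Two regional pairs leave 1 df, t = 12.71, so the half-width is ±14.0, twice the hoped-for difference of 7.

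**6. Using all ten eligible VCs.** One of five treated in each region gives 5 × 5 = 25 allocations and no mirror images, so the smallest P is 1/25 = 0.04. In simulation (100 days per period, variance twice Poisson, all assumed), type I error is about 4%. Power when both intervention VCs double is above 0.99, about 0.90 and about 0.62 at k = 10%, 20% and 30%. If only one doubles, power is about 0.12 to 0.20.

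**The case against.** **The plan does not claim ±1 for the arm difference.** It attaches ±1 to the postintervention mean, ties it to the 14-per-day target and makes that estimate its main statistical aim. This stands. A reader might infer that the 81 days are wrong or that ±1 is invalid, but the documents do not support that. Nor does a stable difference between the two intervention VCs undermine it: averaged over equal days, that difference adds no day-sampling error. Figures at mean 21 would also overstate the loss from overdispersion, because the target is now 14.

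**P<0.05 is not arithmetically impossible.** Only randomisation-based inference is ruled out, and the plan names no such test. A t test with 1 df can reach P<0.05. Ignoring the regional pairing gives 2 df, t = 4.30 and ±4.7 in the example above, which a difference of 7 would exceed. Both results rest on normality of VC-level change, which four VCs cannot verify, and 2 df does not match the paired allocation.

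**The six unselected VCs are not a plan error.** Leaving them out is a design choice. The abstract says that "control VCs will follow existing practices of awareness generation through community activities and health talks", but no section says what the unselected VCs do, so treating them as further controls is an inference. They also lack the study's field monitoring and outreach records.

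None of this rescues a P<0.05 claim based on visit or day counts.

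**Conclusion.** The concern holds for the arm comparison. The article allocates VCs and then sets a significance threshold on a test that ignores VC-to-VC variation in change. The nominal 5% error rate could be anywhere from 13% to 70% over the CVs considered, and the randomisation itself supports no two-sided P below 0.50.

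The CVs, the SD of change and the dispersion are all assumptions, because the article reports no VC-level variation. The 5% rate is right only if all VCs change by exactly the same amount apart from Poisson noise. The allocation count needs no assumption beyond the stated pairing by region.

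The one-arm calculation stands as a description of the selected intervention VCs, given independent Poisson days.

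**What to change.** **(a) Text change, needed in any case.**
- Data Analysis: drop the P<0.05 claim for the arm comparison. Report the difference in change for each of the two regions, descriptively, for these four VCs.
- Sample Size: state that ±1 does not apply to the arm difference. Base the one-arm standard error on the observed dispersion and autocorrelation of the daily counts, not on the Poisson assumption.

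The cost is wording, a less favourable stated precision and the loss of a significance claim that the design cannot support.

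**(b) Optional, if a formal test is wanted.** The sponsor would first confirm that the six eligible unselected VCs followed existing practice, and that the random draw also decided which of the two drawn VCs received the intervention. Then extract their routine walk-in counts for the study months and the same months of the previous year, and use the exact within-region randomisation test over the 25 allocations.

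The cost is data extraction from the VCs' existing management software, with no new fieldwork. There are three downsides. Exchangeability of monitored and unmonitored VCs is an assumption. P<0.05 is reached only if the observed allocation is the single most extreme (P = 0.04). Power is low if only one of the two intervention VCs responds.
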